### Sample size

An estimated 1200 patients are seen at the Norfolk and Norwich University Hospital (NNUH) each year with suspected carpal tunnel syndrome. Of these, at least 85% (around 1020) will be confirmed as having CTS through NCS indicating a mild or worse compression. Assuming a recruitment rate of 75%, which is not unreasonable, given previous experiences, we would expect to recruit around 765 CTS subjects per annum, i.e. 1530 over the two year recruitment period. It is estimated that around 30% (460) will go to surgery immediately and 70% (1070) will be treated with corticosteroid injection. Of the latter, it is expected that, by two years follow-up, two thirds will have been referred for surgery, whereas the remaining third (about 355) will be considered a success. There is no standard agreed method for calculating sample sizes or statistical power for logistic regression models. However, following the approach by Demidenko [24] a sample size of 1070 would confer 90% statistical power, assuming a 33% success rate, to detect an increase in success with an odds ratio of 1.51 for an explanatory binary variable with an even split in classification (i.e. an equal number of subjects in each group). For an uneven split, this odds ratio would be smaller. Should recruitment be less than expected, a sample size of 535 (i.e. half that expected) would confer 90% power to detect an odds ratio of 1.79.

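### The sample size section says an uneven predictor split lowers the detectable odds ratio; it raises it, so power for uncommon predictors is overstated

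*Protocol article*

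**What the plan says.** The Sample size section of the protocol article starts from expected recruitment, arrives at about 1070 patients treated by injection, and works out what that number can detect. It states that "a sample size of 1070 would confer 90% statistical power, assuming a 33% success rate". The effect it has in mind is a raised chance of success, with 1.51 as the odds ratio, and the figure is given "for an explanatory binary variable with an even split in classification". The next sentence reads: "For an uneven split, this odds ratio would be smaller". The section then covers weaker recruitment: "a sample size of 535 (i.e. half that expected) would confer 90% power to detect an odds ratio of 1.79".

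No odds ratio or power figure is given for any uneven split. Nothing elsewhere in the article corrects or qualifies the sentence.

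**The concern.** With a fixed total, the log odds ratio for a binary predictor is estimated about as precisely as possible when the two groups are equal. Shrinking either group adds more variance than enlarging the other removes. An uneven split therefore needs a larger odds ratio for the same power, which is the reverse of what the section says. As written, the sentence implies that 1.51 is a cautious figure which other predictors would improve on. In fact it is close to the best case.

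This bears on the primary aim, which is to identify predictors of treatment response. The Questionnaire data section lists sex, ethnicity, smoking and comorbidity among the factors collected, and the Discussion defends including patients with diabetes partly so that its effect on outcome can be examined. The article gives no cohort prevalences, so it is an assumption that such factors are uneven, though a reasonable one. For sex, the Background rates of 87.8 (men) and 192.8 (women) per 100,000 would give 87.8/(87.8 + 192.8) = 31% men if the cohort mirrored them.

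The Analysis section screens predictors by univariate significance and then applies backward deletion, so a factor with low power is likely to drop out of the model. A reader relying on the sample size statement could take that as evidence of no association.

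**Working it through.** **Inputs from the Sample size section.** N = 1070, or 535 under reduced recruitment; power 90%; success rate 33%; odds ratio (OR) 1.51, or 1.79 at 535; even split.

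**Inputs inferred.** The significance level is not stated with the calculation, and the text does not say whether 33% is the reference-group or the overall rate. A two-sided 5% level with 33% in the reference group reproduces both stated odds ratios. The alternatives do not: one-sided 5% gives 1.45 and 1.69, and 33% as the overall rate gives 1.53 and 1.83.

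**Formulas.** Let f be the share of patients with the predictor, p0 = 0.33 the success rate without it, and p1 the rate with it, where p1/(1 − p1) = OR × p0/(1 − p0). For the Wald test in logistic regression with one binary covariate:

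- Var(log OR) = V/N, with V = 1/[(1 − f) p0(1 − p0)] + 1/[f p1(1 − p1)]
- Power = Φ(log OR / √(V/N) − 1.96)

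**Step 1: reproduce the article's figures at f = 0.5.**

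- N = 1070, OR 1.51: p1 = 0.4265, p0(1 − p0) = 0.2211, p1(1 − p1) = 0.2446. V = 1/(0.5 × 0.2211) + 1/(0.5 × 0.2446) = 17.22. SE = √(17.22/1070) = 0.1269. log 1.51 / SE = 0.4121/0.1269 = 3.248. Power = Φ(3.248 − 1.960) = 90.1%.
- N = 535, OR 1.79: p1 = 0.4685, V = 17.08, SE = 0.1787, ratio 3.259, power 90.3%.

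Solving for exactly 90% power gives 1.509 and 1.785, so both printed values are right for an even split.

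**Step 2: change only the split.** At f = 0.2 with OR 1.51, V = 1/(0.8 × 0.2211) + 1/(0.2 × 0.2446) = 26.10. SE = 0.1562, the ratio falls to 2.639, and power is Φ(0.679) = 75%. Repeating this for other splits, and solving for the odds ratio detectable with 90% power:

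| Share with predictor | Detectable OR, N = 1070 | Power for OR 1.51, N = 1070 | Detectable OR, N = 535 |
|---|---|---|---|
| 50% | 1.51 | 90% | 1.79 (1.785) |
| 40% | 1.52 | 89% | 1.80 |
| 30% | 1.56 | 85% | 1.87 |
| 20% | 1.66 | 75% | 2.03 |
| 10% | 1.94 | 51% | 2.58 |
| 5% | 2.50 | 30% | 3.87 |
| 70% | 1.57 | 84% | 1.89 |
| 80% | 1.68 | 73% | 2.09 |
| 90% | 2.01 | 48% | 2.69 |

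**Step 3: can any uneven split help?** At N = 1070 the minimum lies at f = 0.487, where the detectable OR is 1.5085 against 1.5087 at an even split. The gain is in the fourth decimal.

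**Step 4: the same loss in patients.** The number needed to detect OR 1.51 with 90% power is 1066 at an even split, 1243 at 30%, 1614 at 20% and 2840 at 10%.

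**Step 5: sensitivity.** With 33% as the overall rate, the detectable odds ratios at N = 1070 are 1.53, 1.57, 1.66 and 1.95 for shares of 50%, 30%, 20% and 10%. An ordinary comparison of two proportions gives power for OR 1.51 of 90%, 85%, 75% and 52% at the same shares. The direction is the same in every variant.

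**The case against.** The best textual defence is that smaller might mean further below 1. That would suit a protective odds ratio: the detectable value below 1 moves from 0.64 at an even split to 0.56 at 20% and 0.42 at 10%. The text rules this out, because the sentence refers back to "to detect an increase in success with an odds ratio of 1.51".

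Other objections limit the point without removing it:

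- **No design quantity rests on the sentence.** The sample size comes from expected recruitment, and 1.51 and 1.79 are both correct for an even split. This stands, and it is why the correction is cheap.
- **The overstatement is implied.** No uneven-split power is printed, and the article never calls 1.51 conservative. This stands, but the implication of at least 90% power at 1.51 follows directly from the sentence.
- **The sentence precedes the 535 scenario.** Strictly it qualifies 1.51 only, so its bearing on 1.79 is by extension. The scenario still matters, since the Discussion reports a response rate below expectation.
- **The loss is modest near balance.** At 40% prevalence power is still 89%, and for sex at roughly 30:70 it is about 84–85%. It becomes serious at about 20% or below, or 80% or above.
- **Null results would ordinarily be read from confidence intervals.** That is fair, but it does not make the planning statement true.

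**Conclusion.** The sentence is wrong as written. Under the assumptions that reproduce the article's own figures, 1.51 is in practice the smallest odds ratio detectable with 90% power at 1070 patients, and every materially uneven split needs a larger one. A predictor present in 20% of patients has 75% power at 1.51, and one present in 10% has 51%, about an even chance of detection.

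The exact values rest on a two-sided 5% level, a 33% reference-group rate and a single unadjusted binary predictor. The direction depends on neither the level nor the reading of the 33%. Which candidate predictors are affected depends on prevalences that the article does not give.

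**What to change.** Replace the sentence with one to this effect: for an uneven split the detectable odds ratio is larger, namely 1.56, 1.66 and 1.94 for predictors present in 30%, 20% and 10% of patients at N = 1070, and 1.87, 2.03 and 2.58 at N = 535, assuming a two-sided 5% level and 33% success in the reference group. Those assumptions should stand beside the figures, since the section currently states neither, and the sponsor should confirm that they are the ones used. It is worth adding that predictors present in more than half of patients fare slightly worse than their mirror image (1.57, 1.68 and 2.01 at 70%, 80% and 90% for N = 1070).

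The cost is a sentence or two and less favourable stated figures. No extra patients are needed, and no endpoint or analysis changes.

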### Analysis

The primary outcome (global assessment of outcome) will be modelled using a binary logistic regression model. Predictors will be considered on a univariate basis and those found to have a statistically significant effect on the outcome (at the 10% level) will be entered simultaneously into a multivariable model. A backwards deletion approach based upon change in likelihood will be used to remove those predictors with no significant independent effect. An ordinal logistic regression model will also be considered based upon the proportional odds assumption using the original 5 point ordinal scale as the outcome. However, as the assumption is often difficult to verify, this will be considered as a secondary analysis.

Secondary outcomes will be analysed in a similar fashion using regression models with link functions and error terms appropriate to the distribution of the outcome of interest.

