#### Cost of illness analysis

The resource use data will be used to perform a longitudinal estimate of the cost of illness of carpal tunnel syndrome in the subject cohort over a period of two years from the perspectives of the NHS and society (defined as the sum of NHS and patient out of pocket costs and morbidity-related lost productivity). The total cost of each patient will be calculated as the sum of resource quantities multiplied by relevant unit costs extracted from standard NHS databases (e.g. NHS reference costs and Unit Costs of Health and Social Care). Unit cost sources will be from a common price year, to be determined at time of analysis. Costs incurred in year two will be discounted at 3.5% as per HM Treasury guidelines.

Regression models will be developed as described above to predict cost over two years according to a number of prognostic variables, e.g. symptom severity or functional status at baseline, age, and socioeconomic status. The analysis will make appropriate adjustments to take account of missing and censored data where necessary. Where there are systematic differences between patient self-reported data and primary care records, a secondary analysis will be conducted adjusting primary care cost for any observed bias.

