## Discussion

CTS is the most common nerve entrapment disorder of the upper limb which can lead to considerable hand disability and sickness absence in those working, yet little is known about the cost of CTS to the individual, NHS or society. A range of effective treatment options are available including conservative and surgical interventions. However it is not known which patients are more likely to benefit from what treatment. This prognostic study will provide important information about what baseline factors may predict a good long-term response to conservative treatment and which patients may ultimately require surgery. It is an important first step in building a multivariable model, which can be externally validated in future studies. The value of high quality prognostic research is that it leads to a better understanding of disease progression, better targeting of effective treatments that mitigate progression and allows more reliable information about the risk of a negative outcome to be communicated to patients [15].

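### Choosing predictors by univariable p<0.10 and then backward deletion exaggerates the retained odds ratios and understates their uncertainty: moderately at N=1070, seriously at N=535 and in the surgery group of 460

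*Protocol article*

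**What the plan says.** The rule is written into the protocol article and is not left to a later plan. Under Analysis, "The primary outcome (global assessment of outcome) will be modelled using a binary logistic regression model". Selection then has two stages. First, "Predictors will be considered on a univariate basis and those found to have a statistically significant effect on the outcome (at the 10% level" are carried forward together. Second, "A backwards deletion approach based upon change in likelihood will be used to remove those predictors with no significant independent effect". No removal threshold is given.

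The rule reaches beyond the primary outcome. The same section says "Secondary outcomes will be analysed in a similar fashion using regression models with link functions and error terms" suited to each outcome, and the Cost of illness analysis section says "Regression models will be developed as described above to predict cost over two years according to a number of prognostic variables".

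The Discussion describes the purpose: "It is an important first step in building a multivariable model, which can be externally validated in future studies". The Sample size section powers one predictor at a time: "a sample size of 1070 would confer 90% statistical power, assuming a 33% success rate", to detect "an odds ratio of 1.51 for an explanatory binary variable with an even split in classification". It gives a fallback of 535 subjects with an odds ratio of 1.79, and expects about 460 patients to go straight to surgery.

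**The concern.** The list of retained factors and their odds ratios is the study's answer to its first objective. A factor stays only if its estimate was large enough in this data set to pass two tests. The estimates that remain are therefore, on average, too far from the null. Ordinary confidence intervals are computed as though the model had been chosen in advance.

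The screen also asks a different question from the one that matters. It judges each factor unadjusted, whereas the second stage asks about independent effects. A factor masked by a correlated factor with an opposing effect can be removed before its independent effect is examined.

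At stake is whether later users can rely on the size of the published effects. The smaller sample sizes matter in practice, because the Discussion already reports a response rate below expectation.

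**Working it through.** **1. The plan's own figures.** Wald test on the log odds ratio (OR), 50:50 split, 33% success in the reference group, two-sided 5% level (assumed; the article states none).

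SE = √[(2/N)(1/(p0·q0) + 1/(p1·q1))]; power = Φ(ln OR/SE − 1.96).

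- N=1070, OR 1.51: p1 = 0.4265, SE = 0.1269, 0.4121/0.1269 = 3.248, power 90.1%.
- N=535, OR 1.79: p1 = 0.4685, SE = 0.1787, 0.5822/0.1787 = 3.259, power 90.3%.

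Both stated figures reproduce.

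**2. The stated rule, simulated.** Likelihood-ratio screen at p<0.10, joint entry, backward deletion at 0.05, with 300 data sets per scenario and performance measured in 30,000 new subjects. Assumptions not in the documents: 25 continuous candidates, of which 17 are noise and 8 real; log OR per SD = ln(OR)/2 for ORs of 1.51 (four), 1.3 (three) and 2.0 (one); deletion at 0.05. Success is 33% for injection. For surgery it is 75%, borrowed from the pooled surgical results in the Background. The surgery group is taken to be modelled separately.

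| | N=1070 | N=535 | N=460 (surgery) |
|---|---|---|---|
| Retained log OR ÷ truth, OR 1.51 | 1.09–1.11 | 1.29–1.39 | 1.51–1.57 |
| same, OR 1.3 | 1.40–1.46 | 1.89–1.99 | 2.06–2.32 |
| same, OR 2.0 | 1.01 | 1.04 | 1.12 |
| All candidates fitted, no selection ÷ truth | 0.99–1.06 | 1.00–1.13 | 0.98–1.10 |
| Noise factors kept, of 17 | 0.85 | 0.90 | 0.94 |
| AUC, apparent / new patients | 0.663 / 0.637 | 0.665 / 0.615 | 0.669 / 0.600 |
| Calibration slope, stated rule | 0.83 | 0.68 | 0.57 |
| Calibration slope, unpenalised full model | 0.74 | 0.57 | 0.46 |

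The rows above use independent candidates. With pairwise correlation 0.3 and same-direction effects, the ratios rise to 1.25–1.28 (OR 1.51) and 1.71–1.75 (OR 1.3) at N=1070, and to 1.57–1.64 and 2.33–2.43 at N=535.

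On the odds-ratio scale with independent candidates, a true 1.3 that survives at N=535 appears on average as about 1.3^1.89 = 1.64 to 1.3^1.99 = 1.69. At N=1070 a true 1.51 appears as about 1.51^1.09 = 1.57 to 1.51^1.11 = 1.58.

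**3. Intervals.** A second simulation used 25 candidates, correlation 0.3 and five modest same-direction effects. Retained real log ORs were about 32% too large at N=1070 and 68% at N=535. Nominal 95% intervals of retained terms covered 74% and 66%. A repeat (250 data sets, log ORs 0.15 to 0.20 per SD) gave 30% and 70% for the excess, and 70% and 62% for coverage over all retained terms. Among retained terms that were real, coverage was 93% and 87%. Much of the shortfall therefore comes from surviving noise terms, whose intervals exclude the null by construction.

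**4. Loss of real predictors: power or selection?** The formula in step 1 gives the miss rate of a single 5% test, to set against the loss under the stated rule (independent candidates):

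| | Single test misses | Stated rule loses |
|---|---|---|
| OR 1.51, N=1070 | 10% | about 13% |
| OR 1.3, N=1070 | 46% | 49–54% |
| OR 1.51, N=535 | 37% | 39–47% |
| OR 1.3, N=535 | 69% | 68–73% |

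Most of the loss is power. In the second simulation the screen passed 5.0 of 5 real factors at N=1070 and 4.97 at N=535. Masking needs opposing effects: with correlation 0.2 and mixed signs, a protective factor at OR 1.51 failed the screen in about 75% of data sets at N=1070.

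**5. Penalisation.** In the second simulation, slopes at N=1070 and N=535 were 0.84 and 0.75 for the stated rule, 0.70 and 0.54 for the unpenalised full model, and 1.07 and 1.12 for ridge. New-patient AUC, ridge against stated rule, was 0.639 v 0.636 and 0.634 v 0.625.

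**6. Events per parameter with 25 parameters.** Planned injection group: 355/25 = 14.2. Fallback: 535 × 0.33 = 177, and 177/25 = 7.1. Surgery: 460 × 0.25 = 115 failures, and 115/25 = 4.6.

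**The case against.** The strongest reply has four parts.

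- **The obvious alternative is not better in every respect.** An unpenalised model with all candidates calibrates worse than the stated rule at every size examined, and picking its significant terms exaggerates them about as much. This stands, and it shapes the fix.
- **The screen discards little.** A reader might infer that it throws away real predictors wholesale. The documents do not support that. The earlier surgical study summarised in the Discussion found worse symptoms, function, mental health and physical health all pointing to a worse outcome, and same-direction effects strengthen unadjusted signals. Masking is a risk, not a demonstrated loss. The documents give no correlations among the candidates.
- **The aim is modest.** The article presents the work as a beginning, with prediction rules and external validation to follow, so calibration in new patients is not its stated deliverable. This limits the weight of the slopes. It does not protect the odds ratios, which the first objective does call for.
- **Silence on shrinkage or internal validation is no defect.** A reader might infer that nothing will correct the optimism. An analysis plan may deal with it, and an article may leave it out. The point rests only on the rule that is written down.

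**Conclusion.** The point holds in a limited form. The written rule exaggerates retained effects, and ordinary intervals after selection cover less than 95%. At N=1070 the harm is moderate: about 10% on the log scale for effects near OR 1.51 with independent candidates, 25 to 28% with correlation 0.3, and roughly 30 to 45% for weaker effects (71 to 75% for OR 1.3 under that correlation). Strong effects, with OR about 2, are almost always kept with little distortion. At N=535 and in the surgery group the harm is serious. About one noise factor survives per model, so the retained list is not mostly noise.

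The direction is secure. The sizes are conditional on the assumed number, strength and correlation of candidates, on the 0.05 deletion threshold, on 75% surgical success, and on the survivors being reported with ordinary estimates and intervals. The plan should be changed, but the study's design is not in question.

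**What to change.** 1. Remove the univariable screen.
2. Pre-specify the candidates from the Questionnaire data section and the literature reviewed in the Discussion. Use a shorter list for the surgery group, and for injection if only about 535 are recruited.
3. Report adjusted odds ratios and intervals from the full model for every pre-specified candidate, not only the significant ones.
4. Build the prognostic model by penalised likelihood (ridge or lasso) as the standard method, not as an option for a shorter model.
5. Bootstrap every modelling step, and report an optimism-corrected c-statistic and calibration slope.
6. Apply the same approach, with measures suited to each outcome, to the secondary and cost models.

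No new data or visits are needed, only revised analysis wording and some programming. The price is a less parsimonious model and slightly less favourable reported performance.

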#### Cost of illness analysis

The resource use data will be used to perform a longitudinal estimate of the cost of illness of carpal tunnel syndrome in the subject cohort over a period of two years from the perspectives of the NHS and society (defined as the sum of NHS and patient out of pocket costs and morbidity-related lost productivity). The total cost of each patient will be calculated as the sum of resource quantities multiplied by relevant unit costs extracted from standard NHS databases (e.g. NHS reference costs and Unit Costs of Health and Social Care). Unit cost sources will be from a common price year, to be determined at time of analysis. Costs incurred in year two will be discounted at 3.5% as per HM Treasury guidelines.

Regression models will be developed as described above to predict cost over two years according to a number of prognostic variables, e.g. symptom severity or functional status at baseline, age, and socioeconomic status. The analysis will make appropriate adjustments to take account of missing and censored data where necessary. Where there are systematic differences between patient self-reported data and primary care records, a secondary analysis will be conducted adjusting primary care cost for any observed bias.

### Project timetable

Recruitment to the study began in July 2013 and is due to be completed by July 2015. The two-year follow-up is anticipated to be completed in July 2017.

### Ethical approval

The PALMS study was approved by the East of England/Norfolk Research Ethics Committee (REC reference 13/EE/0106) on 22 April 2013.

## Discussion

CTS is the most common nerve entrapment disorder of the upper limb which can lead to considerable hand disability and sickness absence in those working, yet little is known about the cost of CTS to the individual, NHS or society. A range of effective treatment options are available including conservative and surgical interventions. However it is not known which patients are more likely to benefit from what treatment. This prognostic study will provide important information about what baseline factors may predict a good long-term response to conservative treatment and which patients may ultimately require surgery. It is an important first step in building a multivariable model, which can be externally validated in future studies. The value of high quality prognostic research is that it leads to a better understanding of disease progression, better targeting of effective treatments that mitigate progression and allows more reliable information about the risk of a negative outcome to be communicated to patients [15].

We were faced with a number of design issues that arose during development of the study, not least in the choice of outcome measures. A review of the literature was undertaken to identify those factors which have been shown to be predictive of outcomes for surgical and conservative treatments. Although a number of studies have explored predictive factors these have been conducted either retrospectively, are based on small sample sizes or have been done in the context of randomised trials which has limitations. Katz et al. [25] studied 241 patients enrolled in a community based study of outcomes for CTS treatment. 78% completed follow-up at 18 months. In a bivariate analysis higher pre-operative symptom severity and functional limitations (measured on Boston Carpal Tunnel Questionnaire [26]), lower mental health status and lower physical health status (measured by SF-12) were associated with worse outcome after surgery. Work-related variables associated with a worse outcome after surgery were being in receipt of workers’ compensation and where an attorney was involved, heavy manual labour and those using repetitive forceful exertions. Linear regression identified greater pre-operative functional limitation, tobacco and alcohol use, worse mental health status, prominent day pain and bilateral symptoms as predictors of worse outcome. Those more intensively exposed to keyboard activities had better symptom status. A study by Meys [11] at al examined prognostic factors for response to corticosteroid injection in a prospective cohort study of 118 patients in the Netherlands. Successful outcome was defined as no need for further treatment within 1 year of injection. 67.4% proceeded to surgery by 1 year. Predictors of successful outcome from steroid injection were a lower Boston symptom severity score, lower median nerve ultrasonic cross-sectional area and lower median nerve swelling ratio.

Other putative factors which have been identified in the literature include duration of symptoms, severity of paraesthesia at night [27], constant paraesthesia and older age [28]. Whilst these studies do not offer any definitive answers they have been useful in identifying putative predictors which should be included in our study.

We therefore chose to measure CTS severity, hand functional status, psychological status, overall health related quality of life, co-morbidities, as well as health service resource use and out of pocket costs.

Symptom severity in CTS is normally assessed using the symptom severity subscale of the standardised, disease-specific and patient-reported Levine scale [26] (also called the CTS questionnaire or Boston Carpal Tunnel Questionnaire). It is validated for patients with CTS and has been widely used in trials for conservative and surgical treatment for CTS [29]. Recently a shortened version has been developed by Atroshi et al. [18] and its psychometric properties assessed using both factor analysis and item-response theory (RASCH analysis). It contains 6 items rather than 11 items. We therefore elected to use this version.

Hand functional status can be assessed using the 8-item subscale of the Levine scale, however it has been shown that the items are not specific enough to CTS [18] and other measures of hand and arm disability have been developed since, including the Disabilities of the Arm, Shoulder and Hand (DASH) [30] and Michigan Hand Questionnaire (MHQ) [19]. A limitation of the DASH questionnaire is that the score can be greatly affected by comorbid lower limb disability [31] and it does not generate a separate score for each hand. The MHQ is the only scale which measures function for the left and right hands separately as well as bilateral activities. The MHQ is a 57- item hand-specific outcome questionnaire comprising 6 subscales that measure i) unilateral and bilateral hand function, ii) activities of daily living, iii) pain, iv) work performance, v) aesthetics and vi) patient satisfaction. The MHQ has been shown to be responsive to change in patients undergoing surgical treatment for CTS (effect sizes ranging from 0.6 to 0.9) [32]. The MHQ pain subscale substantially overlaps with the pain questions in the CTS-6 scale and the MHQ aesthetics subscale is not relevant in CTS. The MHQ satisfaction subscale overlaps with the primary outcome measure, the 5 point global assessment of change. We therefore elected to use the remaining 3 subscales of the MHQ in this study, that is, hand function, activities of daily living and work performance.

Resource use data will be collected by self-reported questionnaire. Such data are at risk of recall bias, [33] although patients in general practice appear to be reasonably accurate in estimating GP contacts over a six month period [34]. Use of a diary as an aide memoire will help ensure fidelity of the data. However, to further verify the patient-self-reported data, we will contact at least 10% of patients’ GPs to confirm primary care activity as described above. Records of surgery performed will also be extracted and compared with patient reported data, although evidence suggests that primary care records are a less than ideal source of validation of secondary care activity [35]. Patient recall for secondary care activity is considered fairly reliable [33].

We chose to include patients with diabetes within the study. Patients with diabetes may or may not also have a diabetic neuropathy. However as this is very difficult to differentially diagnose from the CTS, it would be difficult to apply an exclusion criterion for those with diabetic neuropathy reliably. There will also be a large proportion of patients with diabetes and CTS but no diabetic neuropathy. Thus excluding those with diabetes may significantly limit the number of patients who can be recruited, as well as potentially affecting the generalizability of the results. Moreover by including these patients in the analysis it will be possible to examine the effect of diabetes as a comorbid factor on outcome.

We chose to recruit patients through clinical neurophysiology. This has two advantages: firstly, the diagnosis of CTS will be made through a combination of good clinical examination, history taking and NCS, therefore reducing the risk of treatment failures due to misdiagnosis. Secondly, it provides a single point of recruitment for patients referred from primary and secondary care from a large catchment area in Norfolk/Suffolk. Nevertheless, although it was initially planned as a single centre study, initial recruitment data indicates that the response rate is lower than anticipated and further departments of neurophysiology within the UK will be included subject to local research governance approval.

This prospective cohort study will provide information on the course and cost of CTS to the individual, the health service and society as well as identify predictive factors for a good outcome from conservative and surgical treatment. It may guide future development of clinical care pathways for CTS and provide important information to service users and providers on the likely expected outcome from treatment.
